### Data Preparation and Analysis

Quantitative data analysis will be performed using Stata/IC 13.1 (StataCorp LP) with an intention to treat analysis. Missing data for the primary outcome is expected to be minimal as all patient appointments and outcomes are recorded. For the DES and CSQ-8 losses to follow-up will employ last observation carried forward for missing values. Since case BGL data is serial and expected to be nonlinear, case mean of nearby data points imputation will be used for missing data.

Summary univariate statistics will be used to describe the study populations and compare study groups at baseline. Categorical variables will be summarized as raw numbers and percentages and between groups comparisons will utilize chi-square statistics. Multivariate statistical analysis will be performed to compare the groups on primary and secondary outcomes. In addition, survival analysis will be performed to explore time to reach glycemic stability. Statistics will be reported with standard deviations or 95% confidence intervals as appropriate. Statistical significance will be indicated by *P*<.05.

Patient and clinician interviews will undergo thematic analysis supported by NVivo 11 (QSR International). The interview transcripts will be analyzed separately for each participant group using an inductive approach to identify and/or infer themes and codes from the transcripts. Further themes will be classified according to the dimensions of telehealth evaluation framework [41].

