### Population, Setting, and Inclusion Criteria

The first group of participants comprises pregnant women diagnosed with GDM who have commenced insulin therapy to control hyperglycemia. These women attended outpatient GDM clinics at two tertiary hospitals between August 30, 2014, and October 30, 2016, inclusive of follow-up. One hospital is in an outer metropolitan region with a catchment population of significant cultural and linguistic diversity. The other is regionally located and serves a population with a rural background. Combined, the two hospitals have approximately 5000 live singleton births annually, and approximately 800 of the pregnancies are affected by GDM.

Women with GDM (patient participant group) are eligible for inclusion if they have a clinical diagnosis of GDM based on the IADPSG criteria following an oral glucose tolerance test [1]. Other eligibility criteria include gestation up to 35 weeks and access to the Internet via a personal computer, smartphone, or tablet. Prepregnancy glucose intolerance, twin pregnancies, GDM not treated with insulin, and other types of diabetes are exclusion factors.

The second group of participants are Credentialed Diabetes Educator Registered Nurses (CDE-RNs) who provide GDM care at the two centers. The CDE-RNs are directly involved in the RCT component of the study and provide care to women with GDM in the course of their usual practice. The number of these clinicians across the two sites is 8; all are requested to complete the clinician assessments for the study.

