### Sample Size

As an exploratory RCT, a stringent sample size calculation was deemed to be less critical for the TeleGDM trial. Therefore sample size has been set at 100 participants. This determination was largely pragmatic, based on resources, time constraints, the balance of probability for detecting a statistically significant difference in the primary outcome and a reasonable power for secondary outcomes. Estimations based on a finding of 44% fewer clinic visits among those receiving telemedicine versus controls [32] indicated a required sample size of 42 with a power of 0.9 for a similar outcome. Thus if the primary outcome in our study were to be less than the latter cited study, or there was 30% attrition, our set target sample offers good prospects for detecting a difference in the primary outcome.

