### Data and Outcomes

Data for research is collected by the lead researcher. This includes weekly extraction of data from OHP for those in the intervention arm in addition to questionnaire outlined below. For controls, photocopies of patients’ paper diaries are obtained when these patients attend their clinic appointments. In addition to these photocopies, where possible, BGL data are directly extracted from the BGL meter via USB cable connection. Finally, once patients have reached the study end point, they also asked to send outstanding self-monitoring data copies of their diaries via email or as photos via smartphone-based multimedia messaging service.

Demographic data together with diabetes self-efficacy and client satisfaction are collected at baseline with follow-up at least 6 weeks after enrollment in the trial. Self-efficacy and satisfaction are measured using the Diabetes Empowerment Scale–Short Form (DES-SF) [33] (Multimedia Appendix 3) and Client Satisfaction Questionnaire–8 Item (CSQ-8) [34,35] (Multimedia Appendix 4). The DES-SF is a shorter version of the original 28-item questionnaire for measuring self-efficacy in people with insulin- or noninsulin-treated diabetes [36]. The original questionnaire has three subscales: managing the psychosocial aspects of diabetes, assessing dissatisfaction and readiness to change, and setting and achieving goals. The longer version has high construct validity and good reliability [18,36]. The shorter version has 8 items, has high reliability (alpha of 0.85), and the scores were found to change positively with improvement in HbA_1c_ [33]. To minimize the burden on participating women we selected the DES-SF to assess diabetes self-efficacy. The CSQ-8 has been used in diabetes research [37] and was assessed for reliability and validity in a childbirth service evaluation [38]. It is reported to have strong reliability, excellent face validity [34,35], good psychometric properties, high client and staff acceptability, and sensitivity to programs of varying quality [37]. The CSQ-8 is available under paid license while the DES-SF is free with appropriate attribution. Both the DES-SF and SCQ-8 questionnaires are self-completed face-to-face or administered over the phone at baseline and at least six weeks from enrollment. Further information on outcomes and data collection time points is provided in Table 1.

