**Secondary**					
	Clinical measures and satisfaction	Clinician quality of care	Glycemic control	BGL^a^ extraction from OHP^b^; glucometer downloads; patient paper diaries	Enrollment; delivery
			Glycemic stability	Time (days) to BGL stabilization	Between enrollment and delivery
			Insulin adjustments	Time (days) between insulin adjustment	Between enrollment and delivery
			Macrosomia	Fetal ultrasound biometry	2nd (17-22 weeks) and 3rd (>22 wks) trimester
			Diabetes self-efficacy	DES-SF^c^	Baseline; ≥6 weeks
			LGA^d^	Birth weight > 90th percentile	Delivery
			Neonate admission to SCN^e^	Patient medical record	Delivery
			Type of delivery (NVD^f^, LUSCS^g^, other)	Patient medical records	Delivery
			Mother/patient satisfaction with clinical care	CSQ-8^h^	Baseline; ≥6 weeks
					Enrollment; delivery
	Costs	Organization sustainability	Service provider costs	Routine billing administrative data for face-to-face/staff costs; OHP subscriptions	Study exit

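### Last observation carried forward for DES-SF and CSQ-8 can only carry the baseline score forward, because each scale has a single follow-up; it sets change to zero for every woman lost

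*Protocol article*

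**What the plan says.** The Data Preparation and Analysis section fixes the missing-data rule for these two scales: "For the DES and CSQ-8 losses to follow-up will employ last observation carried forward for missing values". It names no alternative method and no sensitivity analysis for them.

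The schedule is given three times, consistently. Data and Outcomes says that the scales "are collected at baseline with follow-up at least 6 weeks after enrollment in the trial", and later in the same section: "Both the DES-SF and SCQ-8 questionnaires are self-completed face-to-face or administered over the phone at baseline and at least six weeks from enrollment" (the second name is evidently the CSQ-8). Table 1 lists the DES-SF and the CSQ-8 each at "Baseline; ≥6 weeks". No measurement between baseline and that follow-up is described.

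Both scales are secondary outcomes. The article plans an intention-to-treat analysis, and its stated hypotheses include greater satisfaction with telemedicine.

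**The concern.** Carrying the last observation forward presupposes some post-baseline observation to carry. Here a woman without the follow-up questionnaire has only her baseline score, completed at enrollment before her care has been supported through the Online Health Portfolio (OHP). The rule is therefore baseline carried forward. For the CSQ-8, a rating of care before telemedicine would be analyzed as a rating of care after it.

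That amounts to assuming, with certainty, that nobody lost to follow-up changed. This sits badly with a trial that expects satisfaction to improve. The between-arm comparison on both scales is at stake: a real effect can be diluted, or a difference can appear because one arm returned fewer questionnaires.

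**Working it through.** **Figure to reproduce.** The article states no effect size, SD or expected loss for either scale. Its one sample-size figure (42, power 0.9) belongs to the primary outcome, so there is nothing to reproduce here.

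**Inputs from the article.** 100 women randomized 1:1, so 50 per arm (Sample Size; Recruitment and Randomization); significance at P<.05, taken as two-sided; one baseline and one follow-up per scale.

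**Assumed inputs.** Changes in SD units, loss of 10% to 40%, baseline to follow-up correlation 0.5, and missingness unrelated to outcome within arm.

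**Formula.** Let cT and cC be the true mean changes in the telemedicine and control arms, and mT and mC the fractions lost. Women who are lost contribute zero change, so

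expected difference under the rule = (1 − mT)·cT − (1 − mC)·cC; true difference = cT − cC.

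**Equal loss m.** The result is (1 − m)(cT − cC). For a true 0.50 SD:
- m = 10%: 0.90 × 0.50 = 0.45
- m = 20%: 0.80 × 0.50 = 0.40
- m = 30%: 0.70 × 0.50 = 0.35

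**Unequal loss, no true difference, both arms +0.5 SD.**
- 10% v 20%: 0.45 − 0.40 = 0.05
- 10% v 30%: 0.45 − 0.35 = 0.10
- 10% v 40%: 0.45 − 0.30 = 0.15

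If both arms instead fall by 0.5 SD, 10% v 40% gives −0.45 + 0.30 = −0.15, so the sign reverses.

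**Unequal loss with a true effect.** Changes of 0.7 and 0.2 SD with 40% v 20% lost: 0.60 × 0.7 − 0.80 × 0.2 = 0.42 − 0.16 = 0.26, against a true 0.50.

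**No bias.** If cT = cC = 0, the result is 0 whatever the loss. If cT = cC and mT = mC, it is also 0.

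**Simulation** (ANCOVA on baseline, 50 per arm, 4,000 trials per scenario; figures varied slightly between runs):

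| Scenario | Baseline carried forward | Observed follow-ups only |
|---|---|---|
| True 0.50 SD, 10% lost in each arm | 0.45 SD, coverage about 94% | 0.50 SD, 95% |
| True 0.50 SD, 30% lost in each arm | 0.35 SD, coverage about 83%, power 60% | 0.50 SD, 95%, power 65% |
| No difference, both +0.5 SD, 10% v 20% | type I error about 6% | – |
| Same, 10% v 30% | type I error 9–10% | 5% |
| Same, 10% v 40% | type I error 15% | 5% |
| No change in either arm, 30% lost in each | type I error 5% | 5% |

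At 30% equal loss the mean standard error under the rule (0.155) matches the empirical SD of the estimate (0.155). The drop in coverage there comes from the shifted estimate.

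**The case against.** The best defense is that the harm is conditional and its size unknown. That stands. There is no bias if neither arm changes on average; with no mean change and 10% v 40% lost, 6,000 simulated trials gave a type I error of 5.2%. At 10% equal loss the distortion is small. These are secondary scales in a self-described exploratory trial, and the primary outcome is untouched. The performance of the observed-data analysis in the table is partly built in, because missingness was simulated as unrelated to outcome within arm.

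Several stronger readings are tempting but not supported:

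- **That 30% is the plan's expected loss for these scales.** The Sample Size section raises it only as a hypothetical for the primary outcome: "or there was 30% attrition, our set target sample offers good prospects for detecting a difference in the primary outcome". No questionnaire loss rate is given.
- **That missingness is built in.** The entry rule reads "Other eligibility criteria include gestation up to 35 weeks", and 35 + 6 = 41 weeks, so the earliest follow-up for the very latest entrants falls around or after delivery. But the window has no upper limit and phone administration is allowed, so delivery does not itself cause a missing score.
- **That telemedicine women will be better followed.** OHP messaging offers an extra contact route, but telephone contact is listed too, and controls are met at clinic and approached again at study end. Unequal loss is possible, not shown.
- **That the rule always favors the better-followed arm.** This holds only if scores rise.
- **That the confidence interval is simply too narrow.** It is narrower than the observed-data interval, but in the scenario examined it reflects the estimator's own variability correctly; the estimate is what is displaced.

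A stray time-point line naming enrollment and delivery follows the CSQ-8 row of Table 1. It names no outcome or instrument and may be an artifact of text extraction. Read as a further CSQ-8 assessment, it would contradict Data and Outcomes, and it would not affect the DES-SF.

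Nothing here makes the rule suitable. Leaving the choice to an unseen analysis plan is no answer either, since the article itself fixes the method.

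**Conclusion.** The point holds as a defect in a stated analysis rule. With one follow-up per scale, the prescribed method is baseline carried forward, and it gives an unbiased between-arm comparison only in special cases or where errors happen to cancel. This follows from the article's text alone.

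The size does not. Under the stated assumptions it runs from slight (0.50 SD read as 0.45 SD; type I error about 6%) to material (0.50 SD read as 0.35 SD with about 83% coverage; type I error 15%). Direction is toward zero with equal loss and can be either way with unequal loss. The article does not show which case will apply. The correction should be made, but it bears on two secondary outcomes and not on the trial's main comparison.

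**What to change.** Delete last observation carried forward for the DES-SF and CSQ-8. In its place, specify one of:

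- a baseline-adjusted likelihood analysis of the follow-up score (ANCOVA or a constrained longitudinal model); or
- multiple imputation using arm, baseline score, risk stratum, site and gestation at enrollment.

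ANCOVA on observed follow-ups alone is adequate only if missingness depends on nothing beyond arm and baseline score. In either case, add a delta-shift sensitivity analysis in which the scores of women lost are moved by a range of amounts, separately by arm, and report the number missing in each arm.

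Follow-up timing need not change. Tying it to the last antenatal clinic contact would make it depend on attendance after randomization, which the intervention aims to reduce.

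The cost is a change to one sentence, made while analysis was still pending, and a little more analysis work. Confidence intervals will be wider: at 30% equal loss the standard error is 0.208 rather than 0.155. Power does not move in one direction. In that scenario it is 65% against 60% under the current rule. With changes of 0.7 and 0.2 SD and 20% v 40% lost, it is 66% against 79%.

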**Figure 2 figure2:**
[figure not shown]
Diary view format introduced after modifications to enhance usability of OHP.

Upon enrollment, patient participants undergo individual semistructured 30 to 45 minutes induction by the lead researcher or research assistants.

The induction is hands-on and covers the initial set-up with participants practicing all the tasks they are expected to perform independently from then on. Induction covers signing up, logging on, navigating through the OHP Web portal, data entry, messaging, and reviewing data trend/summary graphs. All data entry is practiced using the previous day’s data. Performing BGL self-monitoring, administering insulin, and following dietary advice are part of routine diabetes education and counseling provided by a multidisciplinary endocrinology care team as described under usual care. Participants are also instructed on how to share this health information with the GDM clinicians for the purpose of providing clinical care and with the project lead investigator for research data collection and data management purposes. When required and in order to improve study data collection, the lead researcher may set up automatic reminders on OHP to send reminders every second day to prompt the noncomplying patient to enter data. Activating or setting up automated reminders is not routine but it is targeted for those who fail to perform data entry according to expectations. This avoids inundating those who are compliant with unnecessary reminders.

Participants are asked to enter their GDM self-monitoring data onto OHP daily or every other day in order to minimize backlogs and associated data entry errors. Maintaining a paper diary is optional. Automated alerts about new data entries are sent to the clinicians via email prompting the clinicians to log in under their credentials to review the patient data. When required and depending on the reviewed data or patient queries, clinicians provide feedback to the patient via the messaging service about any necessary alterations to treatment (eg, insulin titrations, changes to diet). The CDE-RNs act as the gatekeepers to interact with the telemedicine system and to consult or liaise with other GDM service team members. Patients can also email or print reports for other interested parties who do not have direct access to the Web-based shared data.

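### Neighbor-mean filling of missing BGLs understates variability and, with arm-specific capture, can create a false arm difference in glycemic control and time to stability

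*Protocol article*

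**What the plan says.** The protocol article, Data Preparation and Analysis, describes BGL data as serial and expected to be nonlinear, and on that ground states that "case mean of nearby data points imputation will be used for missing data". It gives no window or maximum gap and does not separate pre- from postprandial readings. The same section plans a survival analysis of time to glycemic stability. Table 1 lists this secondary outcome as "Time (days) to BGL stabilization" and does not define stability.

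Capture of BGLs is described by arm under Data and Outcomes. For the intervention, "This includes weekly extraction of data from OHP for those in the intervention arm". For controls, photocopies of "paper diaries are obtained when these patients attend their clinic appointments", and "where possible, BGL data are directly extracted from the BGL meter via USB cable connection". Under Telemedicine (Intervention), the lead researcher may have the portal "send reminders every second day to prompt the noncomplying patient to enter data", and keeping a paper diary is optional in that arm.

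Usual Care (Control) specifies four readings a day, one preprandial and three postprandial, with targets of 5.0 and 6.7 mmol/L respectively.

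**The concern.** The mean of several readings varies less than one reading. Each filled value makes a woman's series look smoother than it was, and the analysis then treats it as measured. Stability is the property under study, so the filling rule acts directly on the outcome.

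Equal gaps in the two arms would largely cancel in the comparison. The capture routes give reason to doubt equality: a missed portal entry may have no paper backup, while a control reading can be lost with a diary or recovered from a meter. The Introduction itself cites telehealth usage of about 34% to 39%, so sizeable gaps are plausible. If women tend to leave out high readings, their neighbors will usually be lower, and the filled series will look better controlled than it was.

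At stake are the BGL-based secondary outcomes, which contribute to the hypothesis that less service use does not compromise maternal outcomes.

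**Working it through.** The article gives no figure for missing BGLs or time to stability, so there is nothing of its own to reproduce.

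**1. Variance of a filled value.** For m independent readings, Var(mean) = σ²/m. With 2 neighbors the SD ratio is √(1/2) = 0.71; with 4 it is √(1/4) = 0.50. In simulation with same-meal filling, the SD of day-to-day change fell to 0.87 of its true value at 20% missing and 0.73 at 40%.

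**2. Effect on the arm comparison.**
- From the article: four readings a day, targets 5.0 and 6.7 mmol/L, 100 women at 1:1 (50 per arm), significance level 0.05.
- Assumed: glucose curves, 70 days of follow-up, missing rates, two-sided log-rank test, and filling from the two nearest readings on each side.
- Nearby means either the same meal slot or adjacent readings of any meal.
- Stability means three consecutive days with all readings in target, or with mean deviation from target at or below zero.
- Gaps are random, or twice as likely for above-target readings.
- True glucose is identical in both arms. Each rate rests on 600 replicates, so near 5% the Monte Carlo standard error is √(0.05 × 0.95/600) = 0.9 percentage points.

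Results with 10% missing in one arm and 40% in the other:

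| Stability rule | Filled from | Gaps | Median days, 10% vs 40% | False-positive rate |
|---|---|---|---|---|
| All in target | Same meal | Random | 47 vs 36 | 27.5% |
| All in target | Same meal | High missed more | 44 vs 25 | 94.5% |
| All in target | Adjacent | Random | 53 vs 56 | 5.7% |
| All in target | Adjacent | High missed more | 47 vs 39 | 21.5% |
| Mean deviation | Same meal | Random | 15 vs 15 | 5.7% |
| Mean deviation | Same meal | High missed more | 15 vs 12 | 35.3% |
| Mean deviation | Adjacent | Random | 15 vs 14 | 15.8% |
| Mean deviation | Adjacent | High missed more | 15 vs 10 | 64.3% |

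At 10% vs 20% missing the rates ran from 4.8% to 16.2%. With 10% missing in both arms they ran from 4.0% to 7.2%, so the inflation comes from unequal gaps.

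**3. Direction.** With a lower assumed glucose plateau, 40% random gaps and the all-in-target rule, mean time to stability went from 32.4 to 24.7 days with same-meal filling, but from 32.4 to 36.3 days with adjacent filling. In the second case a missing preprandial value is filled from higher postprandial ones and judged against the stricter target. Another set of curves gave the same pattern: 39.2 to 29.0 days with same-meal filling, 39.2 to 45.4 with adjacent filling.

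**4. Would observed readings alone be enough?** A simpler model was used: three readings a day, mean 5.8, SD 1.0, target 6.7 mmol/L, 42 days, stability as three days fully on target. Counting only days with at least two observed readings, all on target, moved the mean from 11.4 days (truth) to 27.8 at 50% random missing. With 50% of high and 20% of other readings missing, the observed mean was 5.69 against a true 5.80 mmol/L. Discarding imputation therefore does not by itself remove dependence on completeness or correct for selective omission.

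**The case against.** Several points on the other side stand.

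- **Direction.** It is tempting to infer that the rule always shortens time to stability, most in the arm with more gaps. The article defines neither nearby nor stability, and step 3 shows the sign can reverse.
- **Which arm.** A reader might infer that the intervention arm is favored, or disfavored. The documents do not support either. Low portal entry would put gaps in the intervention arm; lost diaries or fewer visits would put them in the control arm. Table 1 lists meter downloads without naming an arm, although Data and Outcomes describes them only for controls. Outstanding diary data are requested at study end, and clinicians may prompt women who enter nothing. Unequal gaps are plausible, not established.
- **Precision.** A reader might infer that standard errors of the arm comparison are too small. That depends on whether readings or women are the unit of analysis, which the article does not say, and it was not computed here.
- **Stakes.** The primary outcome is service utilization in an exploratory trial. Large for gestational age, ultrasound macrosomia, delivery type and nursery admission do not use filled BGLs.

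The objection that such detail belongs in a fuller plan does not stand: the article names the method, and the named method is the problem.

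**Conclusion.** The point holds in bounded form. Single neighbor-mean filling understates BGL variability and, if gaps differ by arm, can produce a false arm difference in glycemic control and time to stability. The most likely bias is toward earlier stability where gaps are more frequent: in every setting tested in which high readings were missed more often, time to stability shortened as gaps increased. With random gaps the effect ranged from shortening through none to lengthening.

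The false-positive rates of 5.7% to 94.5% at 10% vs 40% missing are illustrations, not estimates for this trial. They rest on assumed glucose curves, missing rates and stability rules. That the sign turns on an unstated window and meal-type rule is a further reason not to use the method. The change should be made before analysis, which the Results section reports as pending.

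**What to change.** - Drop neighbor-mean imputation. Analyze observed BGLs with a mixed model: random woman effect, day, pre- or postprandial, and arm by time.
- Use the meter download as the preferred source in both arms where obtainable, with portal or diary entries as fallback. Report completeness and source by arm.
- Define stability, and do not count imputed values as on-target readings. Because an observed-only rule with a daily minimum also depends on completeness, either treat stability as interval-censored across days with too few readings, or use multiple imputation within meal type.
- Add a sensitivity analysis in which missing readings are assumed higher than observed ones, since the mixed model does not correct for selective omission.

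The cost is revised analysis wording, a few minutes per visit for downloads in the intervention arm, and somewhat wider intervals. Women who have already finished will have no added meter data, so the fallback sources remain necessary.
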